**Table 4 Tab4:**
[figure not shown]
Overview of key time points in the BANG trial

w, week; m, month; T, time point (the superscript number is cumulative across the trial data collection and denotes how many times the outcome is measured during the data collection window, i.e. T_1_ – T_5_ denotes five data collection times points, T_6_ denotes one data collection time point); solid line denotes duration of BANG intervention and expected duration of usual rehabilitation, dashed line denotes time when some participants might be completing usual care rehabilitation because rehabilitation duration is variable, but it is uncommon for rehabilitation to continue beyond 12 months post-operative

For all patient-reported outcomes, participants will receive up to 3 notifications to complete the questionnaire (1 invitation and up to 2 reminders). Administration of all patient-reported outcomes is managed by the trial co-ordinator. The clinical assessment will be performed at each clinical site, at 12 months post-operative. Measurements will be recorded on an electronic template (Additional file 1) for each participant.

#### Clinician-measured knee function

An independent, blinded assessor will conduct the tests. Participants will complete a standardised warm-up for at least 8 min (either stationary bicycle or treadmill run at rating of perceived exertion of between 12 and 16 (around “somewhat hard”) on the Borg scale [40]) prior to the strength and hop tests. For each strength and hop test, participants will complete at least 1 familiarisation trial on each leg, until they feel comfortable to perform the test. The number of familiarisation trials is at the discretion of the assessor. Strength tests will always be performed before the hop tests because of the maximal effort nature of the test. Participants will have a minimum 5-min rest between completing the strength tests and commencing the hop tests. All tests are completed with shoes on. If participants are unable to complete any one or more of the strength or hop tests, the assessor will record the result as not attempted and the reason why.

Each assessor will be trained in standardised measurement of strength and hop performance. Each clinical site has an isokinetic dynamometer for strength testing. Because the strength and hopping tests are performance tests, assessors will provide vigorous feedback to elicit a maximum test result. Each limb is tested separately; the uninjured limb is always tested first. The hop tests are performed with the participant’s hands clasped behind his or her back.

For the strength tests, the starting position is approximately 110° knee flexion. Participants are instructed to repeatedly straighten and bend their knee as hard and as fast as possible, against the resistance of the dynamometer.

For the single and triple hop for distance, the instruction is to stand on the test leg, then to hop as far forward as possible, taking off and landing on the same foot, and with a controlled, balanced landing. On landing, the foot must remain in the same place – no additional hops allowed – for up to 3 s. The participant will complete two trials on the uninjured leg and two trials on the injured leg, with a minimum 20 s rest between trials. The longest distance hopped will be recorded for both limbs.

For the side hop test, the participant stands on the test leg and hops from side-to-side, over two parallel strips of tape placed 40 cm apart, as many times as possible in 30 s. If the foot touches the either strip of tape, the hop is invalid and not counted. Each trial will be videorecorded to assist the assessor to count valid hops. There is a minimum 90 s rest between completing the trial on the uninjured leg and completing the trial on the uninjured leg. Participants complete one trial on each leg. If > 25% of the hops are invalid, the participant will complete a second trial after at least 3 min rest.

### Data management plan

The trial co-ordinator is responsible for administering all research data collection. The trial co-ordinator or research assistant will monitor questionnaire responses and attempt to contact participants via text message if there are missing data. The blinded assessor who completes the 12-month clinical assessment will check the data collection template prior to sending the data to the trial co-ordinator, to ensure there are no missing data. Researchers from the BANG Trial group will check the coded database for missing, implausible and inconsistent data prior to analysis.

The trial co-ordinator and principal investigators will oversee data management and have access to the full dataset. All BANG Trial group researchers will have access to coded data, on reasonable written request. The trial will comply with Swedish data protection law.

#### Monitoring

A data monitoring committee (DMC) will be established according to the DAMOCLES Group recommendations (see Additional file 1 for DMC charter) [41]. The DMC will be independent of the trial investigators. During the period of trial recruitment, interim analyses will be conducted by the trial statistician and provided to the DMC. The DMC will be free to request any other analyses the committee requires, and these analyses will be provided in the strictest confidence.

The frequency of interim analyses will be determined by the Chair of the DMC. However, we anticipate that there might be one interim analysis and one final analysis. The DMC will comprise at least 3 independent committee members (including at least one clinician and one researcher). One or more trial investigators may attend the DMC meetings, but the decision-making is limited to the independent DMC members.

An interim analysis of adverse events (using generalised estimating equations) may be performed when 50% of participants have been randomised and have completed the 12-month follow-up. The interim analysis will be performed by the trial statistician, blinded to treatment allocation, who will report to the DMC. The DMC will have access to the unblinded data and will discuss the results of the interim analysis. The DMC will recommend whether the trial should continue.

#### Harms

Participants report any adverse events – an untoward physical or psychological occurrence with or without an expected causal relationship to the intervention (e.g. deep vein thrombosis, embolism, superficial or deep infection to the index knee, psychological distress, increase in knee symptoms, ligament sprain, muscle strain, meniscus tear) to the trial co-ordinator via electronic questionnaire (open-ended question sent every 2 weeks during the first year of follow-up; we expect usual care rehabilitation to have a duration of approximately 9 months). A serious adverse event for this trial is any untoward physical or psychological occurrence that the trial investigators believe is causally related to the intervention *and* is any of the following: life-threatening, associated with permanent and/or severe disability, associated with prolonged hospitalisation. Serious adverse events will be reported to the regional ethics review board.

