**Methods:**

Participants scheduled for primary ACL reconstruction are recruited prior to surgery from one of six trial sites in Sweden. We aim to recruit 222 participants (111 in each group) for the BANG trial. Participants are randomly allocated to receive either usual rehabilitation care alone or usual rehabilitation care plus the Back in the Game smartphone application intervention. Back in the Game is a 24-week Internet-delivered programme, based on cognitive-behavioural therapy. The primary outcome is return to the preinjury sport and level at 12 months follow-up. The secondary outcomes assess physical activity participation, new knee injuries, psychological factors, quality of life and physical function. Physical activity participation and new injuries are self-reported every two weeks for 12 months, then every 4 weeks to 24 months follow-up. Psychological readiness to return to sport, knee self-efficacy, motivation to participate in leisure time physical activity, knee-related quality of life, and self-reported knee function are also assessed at 3, 6, 9, 12 and 24 months after surgery. A clinical assessment of strength, knee range of motion, effusion and hopping performance is completed by a blinded assessor at 12 months to assess physical function.

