### Outcomes

The primary outcome is the proportion of participants who return to their preinjury sport *and* participation level at 12 months. The secondary outcomes (Table 2, Additional file 1) are measured at clinically-relevant times, and reflect a biopsychosocial approach to outcome evaluation: patient- and clinician-reported knee function, sports participation and new knee injuries for the biological aspect, psychological readiness to return to sport and self-efficacy for the psychological aspect, adherence to the intervention and/or rehabilitation, and a range of baseline characteristics (Table 3, Additional file 1) for the social aspect.

**Table 2 Tab2:** Summary of secondary outcomes

Measurement variable	Aggregation method	Measurement time point(s)
Sports participation	Number of minutes playing (i) contact, pivoting sports, (ii) non-contact, pivoting sports, (iii) non-pivoting sports	Every 2 weeks to 12-months follow-up; every month from 12 to 24 months follow-up
New knee injuries	Proportion of participants who report a new (i) ACL injury, (ii) meniscus injury, (iii) other knee injury or problem	Every 2 weeks to 12-months follow-up; every month from 12 to 24 months follow-up
Psychological readiness to return to sport	Mean or median ACL-Return to Sport after Injury scale [24] score	3, 6, 9, 12, 24 months
Knee-related self-efficacy	Mean or median Knee Self-Efficacy Scale [25] future domain score	12, 24 months
Motivation to return to sport [26]	Median	3, 6, 9 months
Knee-related quality of life	Mean or median ACL-Quality of Life scale [27] score	12, 24 months
Self-reported knee function	Mean or median International Knee Documentation Committee subjective knee form [28] score	6, 12, 24 months
Self-reported knee function	Mean or median Single Assessment Numeric Evaluation [29]	Every 2 weeks to 12-months follow-up; every month from 12 to 24 months follow-up
Functional knee stability	Frequency of giving way episodes	12, 24 months
Knee effusion	Proportion of participants with stroke test [30] score: 0, trace, 1+, 2+, 3+	12 months
Hopping performance [31, 32]	Mean or median limb symmetry index	12 months
Quadriceps and hamstrings strength	Mean or median limb symmetry index	12 months
Adherence to rehabilitation	Number of sessions completed	Every 2 weeks while completing rehabilitation
Adherence to BANG intervention	Number of completed video and audio sessions	6 months

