#### Secondary outcome measures: *new knee injuries*

Participants self-report any new knee problems that have occurred during the registration period (preceding two weeks). We use an ‘all complaints’ definition of injury [37]. Participants describe the problem, and any diagnosis and treatment received (including the clinician and/or institution where diagnosis and/or treatment was provided).

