### Sample size calculation

There are no trials of psychological support interventions aimed to help athletes return to sport following sports injury, so it is difficult to accurately estimate the expected effect size for our trial. We calculated the same size required to detect a between-group difference in return to preinjury sport rate of 20% at 1 year. We assumed a base return to sport rate of 33%, [39] a two-sided alpha of 0.05, beta of 0.2, and a drop-out rate of 15%. The required sample size is 222 participants (111 in each group).

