## Discussion

This protocol outlines how we plan to conduct the BANG trial to assess the efficacy of an Internet-delivered intervention, delivering cognitive-behavioural therapy to address psychological factors including fear, confidence and recovery expectations (Back in the Game app), for improving the return to sport rate following ACL reconstruction. Promoting life-long participation in sport and active recreation is a critical public health priority, especially given physical inactivity is one of the top-five risk factors for noncommunicable disease [1].

Sustaining injury is often a consequence of playing sport. Some injuries, like a minor ankle sprain, might result in minimal time lost from sport – the athlete quickly resumes normal training, and continues to participate as before her injury. Other injuries require an extended period of the sidelines of sport. ACL rupture is one of the most common sports-related knee injuries, and injured athletes regularly spend at least 12 months on the sidelines of their sport. Some athletes may never regain their enjoyment for participating in sport after serious injury; many fear sustaining the injury again if they go back to their sport [9]. For some athletes, serious injury may be the catalyst for retiring from sport.

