### Issues related to adverse events

The most serious short-term negative consequence after ACL reconstruction and return to sport, is another serious knee injury (ligament rupture or meniscus tear). Sports exposure is the strongest risk factor for new knee injury; 1 in 5 young athletes who returned to sports after ACL reconstruction sustained a second ACL injury [48]. Given the Back in the Game app is designed to improve the return to sport rate after ACL reconstruction – a key patient-important outcome after surgery – there is a possible risk of paradoxical harm. It is within the DMC’s purview to examine adverse events, including new knee injuries, and make recommendations to protect the safety of participants.

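### The adverse event question ends at 12 months while follow-up runs to 24, so non-knee and psychological harms are not prompted for in year 2

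*Protocol article*

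**What the plan says.** The Harms section of the protocol article defines an adverse event broadly: physical or psychological, whether or not a causal link to the intervention is expected. Its examples include psychological distress, ligament sprain and muscle strain. Collection is by electronic questionnaire, an "open-ended question sent every 2 weeks during the first year of follow-up". The same parenthesis adds that "we expect usual care rehabilitation to have a duration of approximately 9 months". No other reason for the 12-month limit is given.

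The rest of the follow-up is longer. The abstract states: "Physical activity participation and new injuries are self-reported every two weeks for 12 months, then every 4 weeks to 24 months follow-up". Table 2 gives the schedule for both sports participation and new knee injuries as "Every 2 weeks to 12-months follow-up; every month from 12 to 24 months follow-up". For new knee injuries, "We use an ‘all complaints’ definition of injury".

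The section on adverse event issues in the Discussion explains the feared mechanism: "Sports exposure is the strongest risk factor for new knee injury", and an app meant to raise the return rate could therefore do paradoxical harm. The harm it names is a further serious knee injury.

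**The concern.** A harms window should cover the period in which the intervention could plausibly cause harm. Here the pathway runs through return to sport, and the protocol's own remarks place much of that late. The Discussion says that "injured athletes regularly spend at least 12 months on the sidelines of their sport", and for the control arm the Sample size calculation says "We assumed a base return to sport rate of 33" (per cent). If the app works, the arms will differ in sport exposure during year 2, after the general adverse event question has ended.

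At stake is the breadth of the harms data. The report could set a 24-month account of sport participation and knee injury beside a 12-month account of everything else. For a psychological intervention, the loss of any prompt about distress in year 2 is worth noting: the Hospital Anxiety & Depression Scale appears only among the baseline measures (Table 3; Data collection) and not in Table 2.

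**Working it through.** **1. Coverage, side by side**

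| Item | Months 0–12 | Months 12–24 | Source |
|---|---|---|---|
| Open-ended adverse event question | every 2 weeks | none stated | Harms |
| New knee injury | every 2 weeks | every 4 weeks or monthly | Abstract; Table 2 |
| Minutes of sport | every 2 weeks | every 4 weeks or monthly | Abstract; Table 2 |
| Hospital Anxiety & Depression Scale | baseline only | none | Table 3; Data collection |

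The adverse event question covers 12/24 = 50% of follow-up; the knee registration is scheduled across 24/24 = 100%.

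**2. Which listed events fall in the gap**

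Meniscus tear, knee ligament sprain, worse knee symptoms and infection of the index knee are all knee problems, so the all-complaints registration can pick them up in year 2. Muscle strain, sprain outside the knee and psychological distress cannot be reported there. Thrombosis and embolism also lack a prompt, but they add little to an argument about sport exposure. A serious event that does not concern the knee has no stated prompted route after month 12.

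**3. One returner's exposure after month 12**

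The documents give no distribution of return times, so the month of return *t* is an assumption. With return at month *t* (6 to 12) and constant play to month 24, exposure is 12 − *t* months in year 1 and 12 months in year 2. The share after month 12 is 12/(24 − *t*):

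- *t* = 6: 12/18 = 67%
- *t* = 8: 12/16 = 75%
- *t* = 9: 12/15 = 80%
- *t* = 10: 12/14 = 86%
- *t* = 12: 12/12 = 100%

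**4. The difference between arms**

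Inputs from the Sample size calculation: 33% control return, a 20-point difference, 111 per arm. The planned size reproduces: 33% v 53%, two-sided alpha 0.05, 80% power and pooled variance without continuity correction give 96 per arm, and 96 × 1.15 = 110.4, rounded up to 111 (222 in total). Dividing by 0.85 instead gives 113 per arm; the difference does not matter here.

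Extra returners at the design effect: 0.20 × 111 = 22.2 (0.20 × 94 = 18.8 after 15% drop-out). The share of their exposure after month 12 then depends on assumptions alone:

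- Returns spread evenly over months 6–12, gap held through year 2: year 1, 22.2 × 3 = 67 person-months; year 2, 22.2 × 12 = 266; share 266/333 = 80%.
- Returns over months 9–12, gap held: 12/(12 + 1.5) = 89%.
- Returns over months 6–12, gap closing linearly to zero by month 24: year 2, 22.2 × 6 = 133; share 133/200 = 67%.
- Under the months 6–12 assumption, the share drops below half if less than 3/12 = 25% of the gap persists on average through year 2.

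The 22.2 cancels from every share, so the protocol's return rates and sample size do not determine the result.

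**5. Look-back**

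The section on new knee injuries describes the registration period as the preceding two weeks, while year-2 registrations come every 4 weeks or monthly. If a two-week look-back were carried into year 2, coverage would be 13 × 2/52 = 50% or 12 × 2/52 = 46%. The article does not say whether it is carried over. Any question added in year 2 should therefore state its look-back.

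**The case against.** The 12-month limit can be defended. App access is active for 24 weeks and then read-only to 12 months (Table 1), and the primary endpoint is at 12 months, so the window covers all use of the intervention and matches the main result. A serious adverse event must, by definition here, be judged causally related to the intervention. The harm the protocol fears most is followed for the full 24 months: knee registrations are checked, with participant contact or record review where needed (Reclassifying variables), analysed by arm (time-varying analyses), and open to the data monitoring committee. Minutes of sport are recorded on the same schedule.

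Most of this stands. A reader might infer that harms collection stops at 12 months, or that the exposure pathway goes unmonitored; the knee registration rules out both. A reader might also take rehabilitation length as the stated reason for the limit, but the text only places the two side by side. Nor can 80% or 89% be presented as the protocol's own figure for the between-arm excess: it rests on assumed return months and on no catch-up by controls, and it counts all sport exposure although the main harm of that exposure is recorded throughout.

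What the defence does not answer is why the remaining adverse events should go unasked in year 2. Sport exposure follows return to sport, not app access, and the registrations are being sent anyway.

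**Conclusion.** The point holds in a limited form and is minor. In months 12 to 24, muscle strain, sprain outside the knee and psychological distress, which the Harms section treats as adverse events, have no prompted collection, and neither do serious events of those kinds. Part of any extra exposure due to the app falls in those months. For an individual returner the share is 67% to 100%, assuming return between months 6 and 12 and continued play; the between-arm share also depends on year-2 catch-up and cannot be fixed from the document.

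The documents do not support predicting that the trial will wrongly report no difference in harms. They support only this: a finding on non-knee or psychological harms would describe the first 12 months. The year-2 registration form itself is not shown; if it already carries the adverse event question, only the Harms text needs correcting.

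**What to change.** In the Harms section, continue the same open-ended adverse event question in the 4-weekly or monthly registration already sent from 12 to 24 months. Word it to cover the whole interval since the last registration, and handle serious events as in year 1. Report adverse events by arm separately for 0–12 and 12–24 months.

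If this is not done, state in the protocol and the trial report that conclusions on non-knee and psychological harms apply to the first 12 months only.

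The cost is one extra question in 12 (monthly) or 13 (4-weekly, 52/4) existing registrations, a short amendment, a small added response burden and some extra coding of free text.

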### Interventions

The Back in the Game app and usual rehabilitation care are summarised according to the Template for Intervention Description and Replication (TIDieR) Checklist [21] (Table 1). All participants complete post-operative rehabilitation as normal. As part of usual rehabilitation care in Sweden, patients typically receive generic written information about knee injury and surgery, recovery in the early post-operative period, return to sport, and injury prevention. A summary of the typical written information patients receive from their treating clinician is delivered to both groups via the smartphone application. The Back in the Game app intervention delivers additional, tailored information and cognitive-behavioural therapy exercises to complement post-operative rehabilitation.

**Table 1 Tab1:** Overview of usual rehabilitation care (control) and the Back in the Game intervention (experimental). All participants receive usual post-operative rehabilitation care

TIDieR item	Control	Experimental
**Name**	Usual post-operative rehabilitation care	Back in the Game plus usual post-operative rehabilitation care
**Why**	Usual care reflects the real-world clinical context. Rehabilitation helps patients recover from surgery, gradually regain knee function, and prepare to return to sport.	Psychological factors such as confidence and anxiety about new injury, have strong influences on returning to sport after serious knee injury. Rationale: supporting psychological readiness to return to sport, in addition to usual rehabilitation, will help athletes transition back to their sport. A self-directed approach will help target the specific challenges encountered by the individual.
**What (materials)**	Strength training equipment (e.g. free weights, machine weights, resistance bands, suspension cables), balance training equipment (e.g. BOSU ball) and aerobic training equipment (e.g. treadmill, stationary bicycle) as available in the usual care setting.	All content is provided on-demand through the Back in the Game smartphone application (see https://vimeo.com/345486299/6bba07cc11 for an overview [in Swedish]).

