### Blinding

Outcome assessors and data analysts are blinded after assignment to intervention. Because the Back in the Game app is a self-directed intervention and designed as a standalone to usual rehabilitation care, there are no additional care givers who should be blind to participant allocation.

Baseline data are collected via the smartphone app, prior to allocation and the intervention commencing. Before they accept participation, all participants are informed that (1) they will receive content guiding them about returning to sport via the smartphone app, and (2) that depending on which group they are allocated to, they will receive more or less content. We do not provide further description of the intervention prior to participants consenting to participate, to avoid inducing participation. Participants are informed that if they agree to be in the trial, there is a 50–50 chance of receiving more than the usual amount of content about return to sport provided during post-operative rehabilitation. Participants are not informed of their group allocation, but we cannot assume they remain blinded to group allocation.

When they return for clinical assessment at 12 months follow-up, we will ask participants not to discuss the amount and content of information they received during post-operative rehabilitation with the outcome assessor. We plan multiple strategies to minimise the chance of a participant inadvertently disclosing allocation to the outcome assessor including sending the participant a reminder SMS message one day prior to the follow-up visit.

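### Serious adverse events as defined cannot be compared between arms, because an event counts only if investigators believe the intervention caused it

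*Protocol article*

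**What the plan says.** The Harms section defines two terms in consecutive sentences. An adverse event is "an untoward physical or psychological occurrence with or without an expected causal relationship to the intervention". Participants report these through an "open-ended question sent every 2 weeks during the first year of follow-up", with no restriction to one arm. A serious adverse event for this trial is "any untoward physical or psychological occurrence that the trial investigators believe is causally related to the intervention" which, in addition, is one of: "life-threatening, associated with permanent and/or severe disability, associated with prolonged hospitalisation". Both conditions must hold. The section gives the serious category one use, which is reporting to the regional ethics board.

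On who is blinded, the Blinding section says: "Outcome assessors and data analysts are blinded after assignment to intervention". It does not mention the investigators who judge causality.

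The Discussion, under adverse events, accepts that because the app is meant to raise return to sport, "there is a possible risk of paradoxical harm".

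**The concern.** Seriousness describes what happened to the participant, while relatedness is somebody's opinion about why. Once the second is a condition of the first, a count of serious adverse events measures attribution as well as harm. In a two-arm trial where only one arm receives the intervention, it also ties one arm's count to zero.

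Two things are at stake. Any tabulation of serious adverse events by arm would be empty or one-sided and could be misread as evidence on safety. And a severe event judged unrelated, in either arm, would carry no seriousness flag and would not reach the ethics board as a serious adverse event. This matters most for indirect harms. If the app acted through changed behaviour, a person judging one case would readily blame the behaviour, and only a count by arm regardless of cause could show an excess.

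**Working it through.** The point is definitional, so the main step is to set the passages side by side. The arithmetic only illustrates it.

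**1. What does the intervention mean?** Harms does not define it, but three other places point the same way.
- Interventions, Table 1, is captioned "Overview of usual rehabilitation care (control) and the Back in the Game intervention (experimental"), so the control arm is usual care and the experimental arm has the intervention.
- Outcomes lists "adherence to the intervention and/or rehabilitation", naming the two as separate things.
- Data collection says that the intervention part of the app is hidden from controls.

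Controls do receive a summary of usual written information through the app (Interventions). That belongs to usual care as the article describes it.

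**2. Consequence for controls.** An event in a participant without access to the programme cannot sensibly be believed to be caused by it. The control count is zero by construction.

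**3. Consequence for the app arm.** A severe event counts only if attributed to the app. The Data management plan gives the principal investigators access to the full dataset, and nothing says that attribution is made without knowledge of arm.

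**4. Denominator.** The only design figure involved is 111 per group. It reproduces: comparing 33% with 53% at two-sided alpha 0.05 and 80% power gives 96 per arm, and 96 × 1.15 = 110.4, rounded up to 111. (Dividing by 0.85 gives 113, close to the stated figure.) The point does not depend on it.

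**5. Illustration.** Let p be the proportion of an arm with an event meeting a severity criterion and a the share attributed to the app. Neither is in the document; both are assumed.
- Serious adverse events counted, app arm: 111 × p × a
- Serious adverse events counted, control arm: 111 × p × 0 = 0
- Severe events regardless of cause, per arm: 111 × p

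With the same p in both arms, so no true difference:

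| p | Severe events per arm | Control count | App count, a = 0 | a = 0.25 | a = 0.5 | a = 1 |
|---|---|---|---|---|---|---|
| 2% | 2.2 | 0 | 0 | 0.6 | 1.1 | 2.2 |
| 5% | 5.6 | 0 | 0 | 1.4 | 2.8 | 5.6 |
| 10% | 11.1 | 0 | 0 | 2.8 | 5.6 | 11.1 |

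The error can also run the other way. If p were 10% in the app arm and 2% in controls but nothing was attributed, the count would read 0 against 0, while the events regardless of cause would be 11.1 against 2.2.

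**6. Which harms are affected?**
- *New knee injuries: not affected.* The Reclassifying variables section sorts them into any new problem, new ACL injury and injury treated surgically, with no causality test. The time-varying secondary analyses compare new knee injury between arms with odds ratios and 95% confidence intervals.
- *Other serious events: affected.* The Harms section's own examples include thrombosis, embolism, infection and psychological distress. Adverse events in general are not in the secondary outcomes of Table 2. Their only stated analysis is the interim one under Monitoring, which may be performed once half the participants have been followed for 12 months.

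**The case against.** The strongest reply is that only the label is affected. Adverse events are collected every two weeks for a year irrespective of cause, so severe ones could be graded and tabulated by arm later. The knee injury that the article treats as the most serious short-term consequence is collected to 24 months and compared between arms without attribution. The DMC has unblinded data, may ask for any analysis and may examine adverse events. Its charter is in an additional file that is not shown, so the tables it receives cannot be judged here.

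Most of this stands, and it rules out several stronger readings that a reader might infer:
- *That serious harms cannot be compared between arms at all.* The all-cause collection and the planned knee-injury comparison show otherwise.
- *That the rule would hide an excess of new knee injuries.* That harm has its own route, independent of the serious label.
- *That the two definitions contradict each other.* A narrow category used for ethics reporting can sit inside a wider one used for collection.
- *That investigator attribution breaches the Blinding section.* That section covers outcome assessors and data analysts. The most that can be said is that attribution is not stated to be blinded.
- *That a falsely reassuring table is planned.* The article describes no table of serious adverse events.

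What the reply does not remove is the rule itself. The article does not say that severe events will be graded regardless of cause, and grading open-ended text afterwards is weaker than classifying events as they arrive. Ethics reporting is tied to the narrow category.

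**Conclusion.** The definition is wrong as written, within limits. Serious adverse events as defined cannot be compared between arms: the control count is in effect 0 of 111, and the app-arm count runs from none to all of that arm's severe events according to attribution. Severe events judged unrelated are not flagged as serious and are not reported to the ethics board as such. The practical loss falls on serious events other than knee injuries. The primary result and the planned knee-injury comparison are untouched.

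This rests on reading the intervention as the Back in the Game programme. That reading is well supported elsewhere in the article, but Harms does not state it. The event rates and attribution shares used above are assumptions, and the conclusion does not need them.

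**What to change.** - Classify seriousness by outcome criteria for every adverse event in both arms, regardless of cause, and name death explicitly among the criteria.
- Record relatedness to the intervention as a separate field, judged without knowledge of arm where possible.
- Tabulate all serious events by arm, for the DMC and in the final report.
- Let reporting to the ethics board draw on the relatedness field as required.

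The cost is revised wording in Harms and one extra field. The fortnightly question already collects the events in the first year, so no new data collection is needed. The downside is a few more events to classify.
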